###### **3. Method**

###### **3.1. Trial Design**

We propose to conduct an open-label trial in which 15 individuals with PTSD receive 1 week of massed CPT combined with a single dose of psilocybin (25 mg) (Figure 1). Participants will meet criteria for a diagnosis of chronic (i.e., at least six months duration) PTSD with a Clinician-Administered PTSD Scale for DSM-5 (CAPS-5) score of 50 or higher. CPT will be provided remotely twice daily (90 minutes total) over the course of a week. On the third day of the intervention, participants will come in for an in-person (6-8 hour) psilocybin dosing session. Participants will receive a total of 12 CPT sessions, 2 psychotherapy sessions related to psilocybin (preparatory and integration sessions), and one psilocybin dosing session over 7 days. The preparatory session will be completed on day 2 of the treatment week and the integration session will be completed a day after the dosing session (day 4). ​​The primary endpoint of this study will be 1 week after the end of the treatment week (week 2). All study visits including therapy sessions and psilocybin session as well as clinical assessments, will be audio and video recorded, with all recordings preserved for research, training, adherence monitoring and quality assurance purposes. We will measure clinician-assessed PTSD symptoms via Clinician-Administered PTSD Scale for DSM-5 (CAPS-5) global severity scores at baseline, the last treatment day (day 7), and at weeks 5 and 13 (follow-up). Additional outcome measures (i.e., self-reported PTSD symptoms, depression and anxiety severity, psychological function, sleep quality) and measures of putative psychological mechanisms of change (e.g., posttraumatic cognitions, experiential avoidance) will also be measured. Participants will be followed-up weekly from week 2 until week 13 (1 week until 12 weeks post-treatment). Participants will use a commercially available wearable device (Oura Ring) to collect passive data that is relevant to mental health and well-being such as physiological signals, sleep and activity patterns. For more details on the study schedule and administration of scales, please see Table 2.

[figure not shown]

**Figure 1.** Study design with timepoints.

######

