###### **3.2.5. Withdrawal Criteria**

Participants are free to withdraw their consent and/or end their participation in the research study at any time without penalty or loss of benefits or treatment to which they are otherwise entitled. Participants may be withdrawn from the study by the study’s doctor if they feel that it is in their best interest.

Participants may also be discontinued if:

- They fail to adhere to the study’s responsibilities;
- The participant meets any exclusion criteria (either newly developed or not previously recognized);
- They present with any AE or unknown allergic reaction to psilocybin;
- Anything, in the opinion of the investigator, that would place the participant at increased risk or preclude the participant’s full compliance with or completion of the study;
- They are pregnant or of childbearing potential and not willing to use an approved method of contraception during the study.

If a participant experiences an AE they will receive the necessary treatments to alleviate any untoward event and will be monitored by the study physician until it is safe for them to be discharged. Participants will be followed up the next day to monitor the progression of their condition. Data from a participant who has been withdrawn will be collected up to the next day after the withdrawal to ensure that the participant has no delayed complications. If a participant withdraws from the study at any time, the reasons for withdrawal will be collected and documented as part of the feasibility outcome for this study. Data collected up to the point of withdrawal will be used for analysis.

If a subject’s participation in the study is terminated prematurely for any reason, the reason for early discontinuation should be thoroughly documented in the case report form (CRF), and the end-of-study assessments should be completed where possible. A termination CRF page should be completed for every participant who receives a dose of psilocybin.

Reasons for a participant’s premature study discontinuation may be categorized as follows:

- Screen Failure: The participant signed the ICF but was deemed ineligible for the study during the screening process;
- AE: An untoward clinical or laboratory event that, in the medical opinion of the investigator, are grounds for early study termination to protect the best interests of the participant. This includes serious and non serious AEs, regardless of their causal relationship to psilocybin;

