###### **6.5. Protocol Deviations**

All protocol deviations will be assessed and documented on a case-by-case basis before the database lock, and deviations considered having a serious impact on the efficacy results will lead to the relevant participant being excluded from the analysis. Protocol deviations will be summarized by center and grouped into different categories, as follows: those who entered the study even though they did not satisfy the entry criteria; those who developed withdrawal criteria during the study but were not withdrawn; those who received the wrong treatment or incorrect dose; those who took any prohibited medications during the study.

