###### **7. Statistics**

###### **7.1. General Procedures and Statistical Methods**

Feasibility outcomes will be reported with descriptive statistics (i.e., counts and proportions). A minimum of 2-3 participants per month (at our single site) will be considered a sufficient recruitment rate to indicate the feasibility of a future larger multi-site trial. We will estimate the proportions of participants adherent with the protocol, that withdraw, and for data completion with a 95% CI. A full trial with this design will be deemed feasible if the lower 95% confidence limit for the rates of adherence and data completion are **≥** 80%, and if the upper limit of 95% confidence interval for the withdrawal rate is ≤ 20%. Frequencies and proportions of AEs and serious AEs will be tabulated for the total sample for each AE type. For continuous outcomes, we will report the means and standard deviations of the score and its change from baseline until the end of treatment and over the follow-up visits. We will estimate the standard deviation of PTSD severity [CAPS-5] and its within person correlation between the baseline and the end of treatment scores. The study will examine the effect size associated with psilocybin-assisted CPT in participants with PTSD, including the durability of effects on PTSD symptoms. The main analysis will be a comparison of PTSD symptoms before and after treatment. There will be analyses of changes in symptoms of depression, psychological functioning, sleep quality and PTSD severity. In week 2, the primary endpoint assessment will take place for all subjects. An independent rater not involved in therapy will administer or collect some outcome measures, and others will be based on subjects’ self-report. Baseline will be compared to the primary end point and follow up time points. This study will provide data on the impact of psilocybin in conjunction with massed CPT. Based on the outcomes, this study will primarily detect effects due to psilocybin-assisted CPT on PTSD symptoms through calculating effect sizes and significance testing. A Wilcoxon signed rank test comparing Clinician-Administered PTSD Scale for DSM-5 (CAPS-5) scores from the baseline to the primary endpoint will be the main analysis. Durability of effects will be examined by comparing changes from baseline to the assessments at 1 until 12 weeks after the final CPT session (day 7) for each PTSD subject using Friedman test, which is a non-parametric test method for repeated measures. Effects on depression symptoms, psychological functioning, trauma-related beliefs and sleep quality will also be assessed for exploratory purposes. Changes in these measures will be compared from baseline to primary endpoint for participants using Wilcoxon signed rank tests. Analyses will examine changes from baseline up to week 13 using Friedman tests. Effect sizes for the psilocybin-assisted CPT will be calculated at the primary endpoint and follow-up time points.

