###### **7.2. Sample Size**

Because the anticipated effect size is unknown, a formal sample size calculation cannot be completed. For this trial, it is anticipated that 15 participants will be recruited.

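### Section 6.5 excludes participants by a deviation's judged impact on efficacy, unmasked and without fixed criteria, which can bias the CAPS-5 comparison upward if exclusions track poor outcome

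*Protocol*

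**What the plan says.** Section 6.5 has two parts. The first sets the process and its consequence. Each deviation is reviewed individually ahead of lock, and the stated consequence is this: "deviations considered having a serious impact on the efficacy results will lead to the relevant participant being excluded from the analysis". The second part lists four categories under which deviations will be summarised, one being "those who took any prohibited medications during the study". Section 6.5 does not say who judges, what they may see when judging, what counts as serious, or which analysis is meant.

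The setting is described elsewhere in the protocol:

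- Section 3.1: "We propose to conduct an open-label trial in which 15 individuals with PTSD" receive the treatment. The Study Summary gives masking as not applicable.
- Section 6.10 gives the coordinator, research assistants, principal investigator and co-investigators access to every source document. Section 10.3.2 makes the investigators the steering committee.
- Section 7.1: a Wilcoxon signed-rank test of CAPS-5 "scores from the baseline to the primary endpoint will be the main analysis".
- Section 7.1, on feasibility: "We will estimate the proportions of participants adherent with the protocol", with a lower 95% limit of at least 80% required.
- Section 3.2.5, on participants who leave: "Data collected up to the point of withdrawal will be used for analysis".

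**The concern.** A participant leaves the analysis because of the believed effect of a deviation on the efficacy result, not because of the type of deviation. Once a deviation exists, that test invites the decider to look at the outcome. In a masked trial, deciding before database lock would give some protection. Here lock hides nothing, because the scores are not masked in the first place.

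Deviations can also be linked to outcome. Section 4.3 bars the listed medications until the end of the study. A participant who is doing badly and restarts one during follow-up becomes a deviator. Because section 6.5 removes the participant and not the affected visits, the earlier week 2 CAPS-5 score would go as well.

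The main efficacy test is at stake, together with the CAPS-5 effect size, standard deviation and within-person correlation that section 7.1 plans to estimate. If the rule also reaches feasibility, it would remove the very participants whom the adherence rate is meant to count.

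**Working it through.** The protocol gives no figure to reproduce. Section 7.2 says that "a formal sample size calculation cannot be completed", and no alpha, power or CAPS-5 standard deviation is stated. The checks below therefore illustrate what the rule could do.

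**1. Efficacy, worst case**

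Inputs from the protocol: n = 15 (section 3.1) and the Wilcoxon signed-rank test (section 7.1). Assumptions: normal change scores with SD 1, improvement positive, true mean change 0 or 0.5 SD, two-sided alpha 0.05.

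Order the scores x(1) ≤ … ≤ x(15) and remove the k lowest. The remaining mean is [x(k+1) + … + x(15)] / (15 − k). There were 20,000 simulated trials for the means and 6,000 for the exact test.

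| Worst k removed | n left | Mean, no true change | Chance of significant improvement, no true change | Mean, true change 0.5 SD |
|---|---|---|---|---|
| 0 | 15 | 0.00 | 2% | 0.50 |
| 1 | 14 | 0.12 | 7% | 0.63 |
| 2 | 13 | 0.23 | 15% | 0.73 |
| 3 | 12 | 0.33 | 25% | 0.83 |

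Removing 1, 2 or 3 participants at random left the mean within 0.005 SD of its true value (0 or 0.5).

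**2. Adherence, only if the exclusion also covers feasibility**

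Take 12 adherent of 15 and remove the 3 non-adherent.

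- All enrolled: 12/15 = 80%. The exact (Clopper-Pearson) lower limit, the p that solves P(X ≥ 12 | 15, p) = 0.025, is 51.9%.
- After exclusion: 12/12 = 100%. The lower limit is 0.025^(1/12) = 73.5%.

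Both fail the 80% rule. With exact limits even 15/15 gives 0.025^(1/15) = 78.2%, and a smaller denominator lowers this ceiling further, so exclusion cannot turn a fail into a pass. Wilson limits behave the same way (79.6% at 15/15).

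Section 7.1 does not name the interval method, and two other methods behave differently. With Jeffreys limits, 13/15 fails (63.7%) and 13/13 passes (82.7%). With Wald limits, 13/15 fails (69.5%) and 13/13 passes with a degenerate 100%.

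**3. Sections 3.2.5 and 6.5 side by side**

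Section 3.2.5 keeps the data of participants who withdraw, and it lists protocol violation, including non-compliance, among the reasons for discontinuation. A participant discontinued for that reason is kept under 3.2.5 but can be removed under 6.5. The two sections meet only in this group, and neither says which prevails.

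**The case against.** The strongest defence is that the rule is narrower than it looks. Five stronger readings are tempting, and the protocol supports none of them.

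- *That the rule biases the result.* A deviation must come first; a poor score alone removes nobody. Exclusions unrelated to outcome do no harm. The direction is not fixed either: a participant who took a barred antidepressant might score better because of it, and excluding that person would lower the estimate. The rule can bias upward, but need not.
- *That the deciders know the scores.* Section 6.5 does not say who decides. Section 7.1 uses an independent rater for some measures, and section 6.10 gives analysts de-identified data only. Neither arrangement makes the decision blind, and the investigators' access to source documents means that nothing prevents outcome knowledge. The documents establish that possibility and no more.
- *That the four categories trigger exclusion.* They are headings for a summary of deviations, not stated exclusion criteria.
- *That adherence will be inflated and the feasibility verdict changed.* The sentence refers to efficacy results, so the efficacy analysis is the more natural reading. With exact limits the verdict does not change in any case.
- *That sections 3.2.5 and 6.5 contradict each other outright.* They overlap only for participants withdrawn for protocol violation.

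It can also be said that analysis sets belong in a statistical analysis plan, which may exist. That is fair as far as it goes. But the protocol does not leave the matter open: it already prescribes an exclusion, and a plan that kept everyone would depart from it.

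**Conclusion.** The concern holds in a limited form. Section 6.5 fixes a mandatory, discretionary exclusion tied to the efficacy result, with no masking, criteria or blinded decider. That permits outcome-driven selection in the main CAPS-5 comparison.

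The shifts of 0.12 to 0.33 SD, and the rise in false-positive improvement from 2% to between 7% and 25%, are upper bounds for 1 to 3 exclusions. They assume normal scores, alpha 0.05 and removal of exactly the worst outcomes. The protocol gives no expected number of deviators and no link between deviation and the lowest scores, so the actual bias may be anywhere from none up to these values.

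The effect on adherence is conditional on reading the rule as covering feasibility. It moves the reported rate but, with exact limits, not the decision.

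This should be fixed. It is not graded higher because efficacy is a secondary objective in an uncontrolled feasibility trial.

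**What to change.** Replace the exclusion sentence in section 6.5 with a statement that no participant is excluded from the main analyses because of a protocol deviation, and define the sets:

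- **Feasibility:** all enrolled participants. Starting this set at Day 1 would lose people who withdraw during the roughly four weeks between screening and the first therapy session.
- **Safety:** all participants from Day 1, when adverse event collection begins (sections 3.10.4 and 4.1.6). A dosed-only set would omit events in people who leave before dosing.
- **Efficacy:** all who start treatment on Day 1 and have data available, with the dosed subset as a supporting analysis.

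List deviations by the existing four categories. Confine any per-protocol set to a sensitivity analysis whose criteria are fixed in advance by type of deviation, not by effect on results. Add to section 3.2.5 that data up to withdrawal are also kept for participants withdrawn for protocol violation.

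The cost is a paragraph of wording and a possibly less favourable estimate. The change is best made before outcome data are seen, because selection made afterwards cannot be reliably undone.

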###### **6.6. Protocol Amendments**

Before any changes to the study are implemented, besides those to eliminate immediate hazards to study participants, an amendment to the study will be reviewed and approved by the REB and Health Canada as applicable.

###### **6.7. Records Management**

Participant records will be distinguished using participant identification (PID) numbers.

Demographic data and active data will be collected electronically through Research Electronic Data Capture (REDCap) separately from the data collected on the Oura App [(92)](https://www.zotero.org/google-docs/?YeAogr). Personal information will be stored at Unity Health Toronto. Demographic and active data will be sent to and stored on a password-protected server maintained by Unity Health Toronto and will be linked by a study participant ID for final analysis. Access to this data will only be granted to study personnel for data management and analysis, as well as database administrators for technical support ([name] – [[contact]](mailto:[contact])).

Research Electronic Data Capture (REDCap; <https://www.project-redcap.org>) software supported by Applied Health Research Centre (AHRC) at Unity Health Toronto, will be used for data collection and overall study data management over the course of this project. REDCap is an open-source, web-based clinical data management and electronic data capture system and database. The system is developed and managed in compliance with Unity Health Toronto privacy, the Health Insurance Portability and Accountability Act, the Personal Information Protection and Electronic Documents Act, and Food and Drug Administration 21 Code of Federal Regulations Part 11 regulations, providing functions such as defined user roles and privileges, user authentication and encryption for in-transit data, de-identification of protected health information and comprehensive auditing features to record and monitor access and changes to data. This system will be used to send scheduled questionnaires to participants and store active data and data monitoring and for the query and export of datasets for statistical analysis and modeling.

Access to REDCap will be secured through a secure web portal and protected by multiple levels of authentication. A project coordinator will be assigned the project administrative privileges for study configuration, data collection management, and quality control.

Participants will use the Oura Ring wearable device to collect passive data. The device and its respective app will have a specific user ID that will be set up by the research team so that the participant remains de-identified on this platform. Data collected from the Oura Ring wearable device will be made accessible through the Oura Application Programming Interface (API) (Oura Teams). Each participant’s data will be exported and de-identified before it is stored on Unity Health Toronto servers, and the data will only be associated with a participant identification number.

The wearable device will collect various parameters related to mental health and wellness, such as heart rate variability (HRV) and the Oura Ring Activity Score. The de-identified data will be stored on Oura servers, with derived metrics extracted and stored within the Unity Health Toronto servers. No personal information will be collected through the Oura digital platform. Only specific members of the project will be able to access the data, which is transferred over the Transport Layer Security protocol layer, hence is by default encrypted by Rivest–Shamir–Adleman algorithm Asymmetric Encryption Algorithm.

The Oura Ring will collect passive and continuous data through its sensors. The raw data will be collected by the Oura app, wherefrom it will be transferred to and stored on its respective server. The digital platform will be set up to comply with de-identification of the data and protection of privacy of the participant. We will use the Oura Application Programming Interface (API) to extract available metrics from their servers and to export the data to be stored on the Unity Health Toronto secure server, with backup on a secure external hard drive located at the Interventional Psychiatry Program. No personal health or clinical information will be shared with Oura.

###### **6.8. Source Documentation**

A wide variety of original documents, data, and records will be considered as source documents in this study. Source data is all information, original records of clinical findings, observations, or other activities in a clinical trial necessary for the reconstruction and evaluation of the trial. Source data are contained in source documents.

Source data include:

REB Documents

- All REB correspondences are documented
- The study staff is REB approved prior to performing any study procedures
- AEs and deviations are reported to the REB per current guidelines and stored appropriately
- All versions of the REB protocols and informed consent forms are on file

Informed Consent

- Ensure that participant identification is not recorded on the ICF (i.e., no participant ID)
- There is documentation that the participant is given a copy of the consent form
- The participant and study representative signed and dated the consent form for themself
- The participant initialed and dated all appropriate pages on the ICF

###### **6.9. Participant Protection**

Participants will not be placed at any risk as a result of the study. Information obtained will be

maintained in a secure and confidential fashion. No participant will be coerced and/or placed

under duress to complete study procedures.

###### **6.10. Confidentiality**

The confidentiality of the data collected and the identity of the individuals participating in this study will be strictly maintained. All files pertaining to subjects in the study will be assigned a unique ID. Personal identifiable information (PII), such as name, address, telephone number, email address, and date-of-birth, will not be accessible to anyone who is not authorized in the study conduct. Only the research coordinator who needs to have direct communications with the participants are authorized to access the PII. Source documents will always be kept in a locked filing cabinet to limit access, and in the case of electronic source documents, files will be password-protected and saved in a secure server. However, our CRFs will not contain any personal health information. Only the unique ID will be recorded in the CRF, and if the subject name appears on any other document (e.g., laboratory report), it must be de-identified and replaced with the unique ID from the copy of the document retained in the Trial Master File or made available for audit.

Study findings stored on a computer will be stored in accordance with Unity Health Toronto data and privacy regulations. The research coordinator, research assistants, Principal Investigator and co-investigators will have access to all source documents collected over the course of the study. Participants will be informed that representatives of other parties (including pharmaceutical companies), Research Ethics Board (REB), or regulatory authorities may inspect their records to verify that all information collected and made available for inspection will be handled in the strictest confidence and in accordance with Unity Health Toronto data and privacy regulations. The investigator will maintain a personal subject identification list (unique ID with the corresponding participant names) to enable records to be identified and retrieved.

Data collected by the Oura Ring will be de-identified on the Oura platform. Each participant’s account on Oura will be created using a dummy email address and password with an associated unique ID. This deidentification will protect participant’s privacy. Subsequently, the data will be transferred to an external encrypted and password-protected hard drive.

During data analysis, de-identified data will be provided to the analysts. This will be achieved using a two-zone approach. The two-zone approach divides study team members into two groups; identified and de-identified. As the names suggest, the identified group will have access to identified (i.e. demographic data) and de-identified information and thus is able to re-identify the data to provide data management, quality and data linkage functions (on active and passive data) whereas the de-identified group will only have access to the de-identified information. This will ensure that the data analysts of the team only have access to de-identified data but will not have access to any of the participant’s identifiers to protect participant privacy.

